## Abstract

**Background:**

Differentiating infection from inflammation in acute pancreatitis is difficult, leading to overuse of antibiotics. Procalcitonin (PCT) measurement is a means of distinguishing infection from inflammation as levels rise rapidly in response to a pro-inflammatory stimulus of bacterial origin and normally fall after successful treatment. Algorithms based on PCT measurement can differentiate bacterial sepsis from a systemic inflammatory response. The PROCalcitonin-based algorithm for antibiotic use in Acute Pancreatitis (PROCAP) trial tests the hypothesis that a PCT-based algorithm to guide initiation, continuation and discontinuation of antibiotics will lead to reduced antibiotic use in patients with acute pancreatitis and without an adverse effect on outcome.

**Methods:**

This is a single-centre, randomised, controlled, single-blind, two-arm pragmatic clinical and cost-effectiveness trial. Patients with a clinical diagnosis of acute pancreatitis will be allocated on a 1:1 basis to intervention or standard care. Intervention will involve the use of a PCT-based algorithm to guide antibiotic use. The primary outcome measure will be the binary outcome of antibiotic use during index admission. Secondary outcome measures include: safety non-inferiority endpoint all-cause mortality; days of antibiotic use; clinical infections; new isolates of multiresistant bacteria; duration of inpatient stay; episode-related mortality and cause; quality of life (EuroQol EQ-5D); and cost analysis. A 20% absolute change in antibiotic use would be a clinically important difference. A study with 80% power and 5% significance (two-sided) would require 97 patients in each arm (194 patients in total): the study will aim to recruit 200 patients. Analysis will follow intention-to-treat principles.

**Discussion:**

When complete, PROCAP will be the largest randomised trial of the use of a PCT algorithm to guide initiation, continuation and cessation of antibiotics in acute pancreatitis. PROCAP is the only randomised trial to date to compare standard care of acute pancreatitis as defined by the International Association of Pancreatology/American Pancreatic Association guidelines to patients having standard care but with all antibiotic prescribing decisions based on PCT measurement.

**Trial registration:**

International Standard Randomised Controlled Trial Number, ISRCTN50584992. Registered on 7 February 2018.

**Electronic supplementary material:**

The online version of this article (10.1186/s13063-019-3549-3) contains supplementary material, which is available to authorized users.

## Background

Overuse of antibiotics and the resultant emergence of multidrug-resistant organisms is a potent threat to the welfare of humanity in the twenty-first century [1, 2]. Acute pancreatitis is an inflammatory disorder of the pancreas with an incidence of 150–420 cases per million [3] and an overall case-fatality rate of 4–6% [4, 5]. In addition to being a significant cause of death, severe acute pancreatitis (SAP) is associated with prolonged critical care occupancy, lengthy in-patient stay and slow rehabilitation [6]. SAP is characterised by necrosis of pancreatic tissue which with bacterial colonisation leads to infected necrosis [7]. Antimicrobial therapy to prevent infection of necrosis in acute pancreatitis has been evaluated in a series of randomised controlled trials, with overall findings demonstrating a lack of benefit reported in meta-analyses and a Cochrane systematic review [8–10].

Correct use of antibiotics is important in patients with infected necrosis but use in those with systemic inflammation in acute pancreatitis is non-therapeutic and possibly harmful [11]. Discriminating between pancreatic infection and inflammation is difficult, with neither clinical assessment nor markers of inflammation (such as leukocyte count or C-reactive protein) being sufficiently accurate [12]. As a result there is overuse of antibiotics for suspected infection in acute pancreatitis, with up to two-thirds of patients receiving at least one course of antibiotics during their admission [13]. Antibiotic overuse in acute pancreatitis is widespread not only in the United Kingdom’s National Health Service (NHS) [14] but also worldwide [15–18]. Overuse of antibiotics in acute pancreatitis is associated with the emergence of resistant organisms, antibiotic-related side effects, compromised treatment efficacy and unnecessary health care costs. Nationally, the National Confidential Enquiry into Patient Outcome and Death (NCEPOD) [19] undertook the largest survey to date of the treatment of acute pancreatitis in the NHS. “Treat the Cause”, published in 2016, recommends better support for clinicians making bedside decisions about the use of antibiotics [19]. Specifically, the report highlights the need for assistance in differentiating infection from inflammation and better evidence for initiation, continuation and discontinuation of antibiotics in acute pancreatitis.

One method of distinguishing infection from inflammation is measurement of procalcitonin (PCT) [20]. Historically, calcitonin peptides were thought to be responsible for calcium homeostasis but this is now thought to be a relatively minor physiological role, and a more contemporary appraisal is that procalcitonin is a “hormokine”, sharing characteristics of both hormones and cytokines and having roles in maintaining vascular endothelial tone in response to bacterial infection [20]. The procalcitonin level in the bloodstream of healthy individuals is below the limit of detection (10 pg/ml) using clinical assays. Procalcitonin levels rise rapidly in response to a pro-inflammatory stimulus of bacterial origin and normally fall after successful treatment [21]. PCT is more sensitive than clinical assessment and routine laboratory markers of sepsis (such as leukocyte count and C-reactive protein) in detecting pancreatic infection [22]. Algorithms based on measurement of procalcitonin have emerged as a means of differentiating bacterial sepsis from a systemic inflammatory response in a wide range of settings [23].

A recent Health Technology Assessment (HTA) report evaluated procalcitonin testing as a guide to antibiotic therapy and concluded that further studies are needed before widespread adoption [24]. PCT has also been evaluated as a biomarker in SAP, mainly for early prediction of severity and for identification of patients with a high risk of infected pancreatic necrosis [25].

Qu et al. [26] reported the results of the only randomised controlled trial of a procalcitonin algorithm in severe acute pancreatitis: a single-centre study of 71 patients from China. They compared a PCT-based algorithm for guidance of antibiotic use to routine care in patients with acute pancreatitis. The duration of antibiotic treatment in the PCT-guided group was significantly shorter (10.9 ± 2.8 vs 16.1 ± 2.5 days, *p* < 0.001) without any adverse effects on outcome. Duration of intensive care treatment, overall hospital stay and cost of care were significantly reduced in the PCT-guided group. However, all patients in the control arm were given antibiotics for up to 14 days, which does not reflect current international guideline recommendations. Thus, the findings of this study need to be reproduced in a setting where antibiotic use follows contemporary practice before procalcitonin-based algorithms can be recommended to guide antibiotic use in acute pancreatitis.

The PROCalcitonin-based algorithm for antibiotic use in Acute Pancreatitis (PROCAP) trial tests the hypothesis that a procalcitonin-based algorithm to guide initiation, continuation and discontinuation of antibiotics will lead to reduced antibiotic use in patients with acute pancreatitis without an adverse effect upon outcome.

## Methods and analysis

### Design

This is a single-centre, randomised, controlled, single-blind, two-arm phase III pragmatic clinical and cost-effectiveness trial. Patients will be allocated on a 1:1 basis to intervention and control. Patients, but not clinicians, will be blind to their allocation.

### Participants

Participants will be patients with a clinical diagnosis of acute pancreatitis admitted to the hepato-pancreato-biliary (HPB) service of the Manchester Royal Infirmary (MRI). The MRI is the regional specialist HPB service for the Greater Manchester and Cheshire region, a conurbation of 3.2 million people. Patients admitted directly to the service and those arriving as tertiary transfers from other hospitals will be included as separate strata within the trial design.

### Inclusion criteria

Adult patients presenting with acute pancreatitis admitted or referred to the service will be involved. All acute admissions are screened for potential trial participants. Inclusion criteria include the following:Patients over the age of 18 years of ageValid informed consentA diagnosis of acute pancreatitis requiring two of the following three features [7]:I.abdominal pain consistent with acute pancreatitis (acute onset of a persistent, severe, epigastric pain often radiating to the back)II.serum lipase activity (or amylase activity) at least three times greater than the upper limit of normalIII.Characteristic findings of acute pancreatitis on contrast-enhanced computed tomography (CECT), magnetic resonance imaging (MR) or transabdominal ultrasonography

### Exclusion criteria

Exclusion criteria include the following [27, 28]:Patients under the age of 18 years of age2.Comorbidities requiring prolonged antibiotic therapy—such as infective endocarditis3.Severely immunocompromised patients—such as those with human immunodeficiency virus and with a CD4 count of less than 200 cells/mm^3^; neutropenic patients (< 500 neutrophils/mm^3^)4.Patients on immunosuppressive therapy5.Previous thyroid surgery

### Intervention

The intervention is the use of a procalcitonin-based algorithm to guide antibiotic use. The algorithm is presented in Table 1. A study flowchart is shown in Fig. 1. Patients will be randomised in a 1:1 ratio to receive algorithm-guided or standard care. The randomisation will be stratified by patient admission route (direct or tertiary referral).

**Table 1 Tab1:** Procalcitonin-based algorithm to guide antimicrobial use in acute pancreatitis

Evaluation only after enrolment at time of admission to hospital		
PCT result	< 1.0 μg/L	≥ 1.0 μg/L
		
Recommendation on antibiotic use	Do not start antibiotics Stop antibiotics in patients already on antimicrobial therapy	Antibiotic intervention (follow Trust guidelines for prophylaxis or treatment)
		
Follow-up	If there is clinical concern about infection, re-check PCT after 24 h	Reassess clinical condition and re-check PCT after 48 h
PCT result	< 1.0 μg/L	≥ 1.0 μg/L
Recommendation on antibiotic use	No antibiotics (or stop antibiotics)	Continue antibiotics (or start if not already on antibiotics) (consider change in antibiotics if clinically indicated)
Over-ruling the algorithm	Empiric antibiotic therapy is permitted in patients not allocated by PCT algorithm to receive antibiotic but decision to be made only by ITU consultant or HPB consultant surgeon and documented in case notes	

*HPB* hepato-pancreato-biliary, *ITU* intensive therapy unit, *PCT* procalcitonin

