**Fig. 2 Fig2:**
[figure not shown]
SPIRIT figure for the PROCAP trial. EQ-5DL EuroQol EQ-5D, PROCAP PROCalcitonin-based algorithm for antibiotic use in Acute Pancreatitis, SPIRIT Standard Protocol Items: Recommendations for Interventional Trials

Patients who become symptomatic (at any point) for infection will undergo PCT assay and follow the PCT algorithm. Clinically symptomatic patients with a low PCT will not receive antibiotics. If there is persisting concern of infection in patients with a low PCT, the test will be repeated at 24 h. Symptomatic patients with a raised PCT will receive antibiotics according to Manchester University Foundation Trust antibiotic policy. The PCT algorithm will be used to guide continuance and discontinuation of antibiotics. In asymptomatic or symptomatic patients with positive microbiology results, it is appropriate to treat positive microbiology results with antibiotics. PCT should be measured before commencing antibiotics. PCT measurement should be used to guide cessation of therapy, either after 48 h, 72 h or 96 h as clinically appropriate. To avoid repeated short courses of antibiotics, if antibiotic use is triggered by the algorithm, use will be continued for at least 48 h and then PCT re-assayed. If there is no clinical evidence of infection at this point, with this second PCT measurement below threshold, antibiotic use will be discontinued. If antibiotics have been prescribed outwith the algorithm, then continued use will be discussed with the consultant hepato-pancreato-biliary (HPB) surgeon under whose care the patient is being treated or with the Chief Investigator. After this discussion, antibiotic therapy may be stopped. The clinician over-ride can be used to either start or stop antibiotics in situations of clinical urgency. Then, the clinician must be either a consultant HPB surgeon or a consultant intensive care physician, and the reason for over-ride will be documented. If patients undergo endoscopic, radiological or surgical procedures which would normally be undertaken under the cover of antibiotic prophylaxis, it is appropriate to do this without PCT measurement. If prophylaxis is merged with therapy, then the PCT measurement for discontinuance will be triggered.

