## Discussion

The PROCAP trial tests the hypothesis that a procalcitonin-based algorithm to guide initiation, continuation and discontinuation of antibiotics will lead to reduced antibiotic use in patients with acute pancreatitis without an adverse effect upon outcome. The trial explores the concept that a potentially clinically relevant study can be undertaken without peer-review funding but can address an important question.

When complete, PROCAP will be the largest randomised trial of the use of a procalcitonin algorithm to guide initiation, continuation and cessation of antibiotics in acute pancreatitis. PROCAP is the only randomised trial to date to compare standard care of acute pancreatitis as defined by the IAP/APA guidelines to patients having standard care but with all antibiotic prescribing decisions based on procalcitonin measurement.

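### Table 1, named as the algorithm, and the intervention-arm text give conflicting rules on positive cultures with a low PCT, running antibiotics, stopping and the over-ride

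*Protocol article*

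**What the plan says.** The Intervention section states: "The algorithm is presented in Table 1". Table 1 has two tiers, each split at 1.0 μg/L.

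- **First tier, PCT below 1.0.** Antibiotics are not started, and any already running are stopped. PCT is re-checked at 24 h if there is concern about infection.
- **First tier, PCT 1.0 or above.** "Antibiotic intervention (follow Trust guidelines for prophylaxis or treatment"), then clinical reassessment and a re-check at 48 h.
- **Second tier.** Below 1.0, no antibiotics or stop; at 1.0 or above, continue, or start if not yet treated.
- **Over-ruling.** "Empiric antibiotic therapy is permitted in patients not allocated by PCT algorithm to receive antibiotic", decided by an ITU consultant or HPB consultant surgeon and documented.

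The Intervention arm protocol (text before and after Fig. 2) adds its own rules.

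- **Testing.** Baseline PCT is measured and the algorithm followed. Ward patients still in hospital are re-tested on days 4 and 7, and critical-care patients daily in the acute phase.
- **Starting.** "Symptomatic patients with a raised PCT will receive antibiotics according to Manchester University Foundation Trust antibiotic policy". Symptomatic patients with a low PCT are to go untreated. Positive microbiology may be treated with or without symptoms, after a PCT sample but with no threshold attached. Procedural prophylaxis needs no PCT.
- **Stopping.** "If there is no clinical evidence of infection at this point, with this second PCT measurement below threshold, antibiotic use will be discontinued". A course prescribed outside the algorithm is discussed with the consultant or the Chief Investigator, after which stopping is optional.
- **Over-ride.** "The clinician over-ride can be used to either start or stop antibiotics in situations of clinical urgency".

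The Discussion describes the algorithm arm as standard care "with all antibiotic prescribing decisions based on procalcitonin measurement", and the abstract says the same.

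**The concern.** The algorithm is the intervention. If the table and the text direct the same patient differently, two clinicians can each follow the protocol and act in opposite ways. The primary outcome is whether any antibiotic is used during the index stay, so a disagreement over starting can decide a patient's result. The Analysis plan promises sensitivity analyses of protocol adherence, and the Data Monitoring Committee is to consider adherence. Neither can classify a patient for whom following one rule breaks the other. A reader of the results would also not know which algorithm had been tested.

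**Working it through.** No arithmetic settles this, so the two sources are set side by side.

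| Situation | Table 1 | Intervention arm protocol | Reading |
|---|---|---|---|
| (a) Positive microbiology, PCT below 1.0 | Do not start; stop if running | Treatment is appropriate, yet symptomatic low-PCT patients are to go untreated | Conflict with Table 1, and tension within the text |
| (b) Antibiotics already running, PCT below 1.0 | Stop | If prescribed outside the algorithm: discuss, then stopping is optional | Conflict |
| (c) Second PCT below 1.0 | Action cell: stop, on PCT alone | PCT below threshold and no clinical infection | Conflict in the stated condition |
| (d) Consultant over-ride | Covers giving antibiotics; no urgency condition | Covers starting or stopping; clinical urgency required | Different scope and condition |
| (e) Raised scheduled PCT, no symptoms | Treat; no symptom condition | Rule stated for symptomatic patients only | Unclear, not contradictory |

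On (e), the case must be expected, because testing is scheduled and not only prompted by symptoms. Table 1 is headed as an evaluation at admission, so it does not itself say what a raised day 4, day 7 or daily value triggers in a patient who is well.

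**Which outcome each item can move.** The primary outcome is binary, so only rules that decide whether a patient receives any antibiotic can change it.

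- Starting rules can: (a) in an untreated patient, (d) when used to start, and (e).
- Item (b), or (a) when a course is already running, can matter in a patient who arrives on antibiotics. The Outcomes section leaves pre-admission prescriptions out of the primary endpoint, so the result may turn on whether the course continues after admission. This assumes that continuation counts as use during the index stay.
- Item (c), and (d) when used to stop, come after antibiotics have been given in the stay. They cannot turn a yes into a no; they mainly change days of antibiotic use, a secondary outcome.

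**The sample size is not in dispute.** With 60% against 40%, two-sided 5% and 80% power, the pooled-variance formula gives n = [1.960 × √(2 × 0.5 × 0.5) + 0.8416 × √(0.24 + 0.24)]² / 0.20² = (1.386 + 0.583)² / 0.04 ≈ 96.9, so 97 per arm, as the Sample size section states. That section rests the 20 points on clinical importance and on other algorithm trials. The 40% therefore presupposes neither reading of the start rule.

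**The case against.** The best defence is that the text elaborates on Table 1, and much of this stands.

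- **Starting.** A reader might infer that the text forbids antibiotics in an asymptomatic patient with a raised PCT, and so contradicts Table 1. It does not. The sentence belongs to a block on patients who become symptomatic, and the baseline test follows the algorithm without any symptom condition. What remains is silence on the later scheduled tests.
- **Re-testing.** A reader might also infer a clash between 48 h in Table 1 and "PCT measurement should be used to guide cessation of therapy, either after 48 h, 72 h or 96 h as clinically appropriate". That sentence follows directly on the positive-microbiology sentences and can be read as confined to them. For a course triggered by the algorithm, both sources give a re-assay after 48 h. The ward and critical-care schedules are likewise elaboration.
- **Stopping.** Table 1 calls for clinical reassessment before the second PCT. This narrows (c), but the action cell still states PCT alone.
- **Over-ride.** Table 1 does not prohibit over-ruling in order to stop, and both sources name the same two kinds of consultant. The difference in scope and in the urgency condition remains.
- **Power.** It is tempting to assume that the ambiguity raises antibiotic use in the algorithm arm by some number of points and to quote the lost power. The document gives no rate for any of these routes, and the net effect could run in either direction. Such a figure would show only that smaller differences have less power.
- **Validity.** The analysis is by intention to treat regardless of compliance, so the randomised comparison itself is not invalidated.
- **Unseen material.** The two figures and the full protocol are not shown and may set out a single pathway. The article would still contradict itself.

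The defence does not remove (a), (b), (c) or (d).

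**Conclusion.** The point holds in a bounded form. Table 1 and the intervention-arm text conflict on four matters, and the handling of a raised scheduled PCT without symptoms is unclear. This is more than missing detail: under (a) and (b) the same patient gets different instructions, and (c) and (d) attach different conditions to the same decision.

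The effect on the primary endpoint is limited to starting rules and to continuation in patients arriving on antibiotics; elsewhere it falls mainly on days of use. Neither its size nor its direction can be derived from the document. The firm consequences are an intervention that is not described as one rule set and adherence that cannot be scored for the affected patients.

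The statement that all prescribing in the algorithm arm rests on PCT is inaccurate as a description, given the microbiology and prophylaxis routes. It is a summary and not an operating rule, so correcting it is editorial.

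**What to change.** 1. The investigators should reconcile Table 1 with the Intervention arm protocol into one set of rules for starting, stopping and over-riding. It should cover positive microbiology with a low PCT, courses already running at admission or prescribed outside the algorithm, and a raised scheduled PCT without symptoms. It should also say which courses the 48, 72 or 96 h sentence applies to. Which clinical rule applies is for the investigators.
2. Score adherence, for the planned sensitivity analyses and the Data Monitoring Committee, against that single version.
3. Align the abstract and the Discussion with the routes to antibiotics that do not depend on a PCT threshold.

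The cost is a protocol clarification and the re-issue of any ward copy of the algorithm. No extra data and no change to the sample size are needed.

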**Fig. 1 Fig1:**
[figure not shown]
PROCAP study flowchart

### Intervention arm protocol

This protocol is summarised in the SPIRIT Figure (Fig. 2). Patients in the intervention arm of the trial are clearly identified by a trial sticker in the case notes and drug kardex. Baseline PCT will be measured on admission (day 0) and the algorithm followed. For patients admitted to ward-based care, PCT will be routinely re-assayed on day 4 and at day 7 after admission for those patients remaining in hospital to these time points. Venesection for PCT assay will be undertaken at the same time as venesection for routine clinical blood tests: no additional venesection is required for PCT measurement. For patients admitted to the critical care unit, PCT will be measured daily during the acute phase of their illness.

